### Adjudicating outcome variables

All the physicians who evaluate the clinical and laboratory postoperative course will be blinded to the group allocation. Postoperative pain will be evaluated by APU physicians. The presence of postoperative complications and the C–D classification will be assessed separately by two teams of investigators (thoracic surgeons and anesthesiologists) at hospital discharge. In cases of discrepancy, there will be a meeting between both teams to discuss the results and reach an agreement. In this meeting between researchers, the complications collected will be assessed to determine if they meet the criteria for their diagnosis, and those that meet the definition criteria will be recorded as a complication while those that do not meet the definition criteria will not be evaluated.

Length of stay in the hospital and PACU, readmission, and mortality at 30 days will also be recorded by the investigator team based on the hospital electronic register.

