Lidocaine is the only local anesthetic (LA) that is safe for intravenous (IV) use. We have known for years that IV lidocaine has systemic analgesic effects, and its intravenous administration intraoperatively decreases opioid consumption. Anti-inflammatory effects associated with the use of local anesthetics have also been described [13]. The use of a continuous IV infusion of lidocaine during surgery is associated with a lower systemic inflammatory response according to plasma cytokine levels, as well as less postoperative pain, a shorter duration of postoperative paralytic ileus, and earlier hospital discharge [14–17]. At the experimental level, our group demonstrated that administration of IV lidocaine in pigs subjected to LRS (lobectomy) decreased proinflammatory cytokine expression in the liver and bronchoalveolar lavage (BAL) fluid, and it also decreased pulmonary edema [18, 19]. These effects were observed both intraoperatively and at 24 h postoperatively. We hypothesized that IV or paravertebral (PV) administration of lidocaine would attenuate the systemic and pulmonary inflammatory response that patients usually develop, which would result in a better postoperative course.

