#### Outcomes

##### Primary outcome

The primary outcome is the proportion of patients included in the different scales of the Clavien–Dindo (C–D) classification [20] in the three groups of patients. The greater the intensity of the treatment that is necessary to correct any postoperative complication, the higher the C–D classification will be considered. Any deviation from a normal postoperative course will be classified into grade I, II (minor complications), IIIa, IIIb, IVa, IVb, and V (major complications) of this classification (Appendix 1).

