##### Secondary outcomes

Secondary objectives including the following will be the comparison between three groups of patients with the following laboratory or clinical data:

Secondary clinical outcomes
Postoperative pain intensity: Postoperative pain will be evaluated using the VAS at rest, during movement, and when coughing during the stay in the PACU and in the two days after. We will also record the doses of self-administered rescue analgesics by PCA pump during the first 48 h after surgery, as well as the cumulative morphine consumption in the first 48 h post-operation.Postoperative pulmonary complications (PPCs): PPCs will be classified using the definition applied in the ARISCAT study [21] (atelectasis, suspected pulmonary infection, respiratory failure, bronchospasm, aspiration pneumonitis, pleural effusion, and pneumothorax; Appendix 2). Because pneumothorax and pleural effusion are the usual outcomes after LRS in the nondependent lung, we will consider them to be complications only if they occur in the dependent lung. The time frame is up to 30 days after intervention.Postoperative cognitive dysfunction (POCD) is defined as the presence of a mini-mental test value less than 27 points at 3 days postoperative (in patients with a value of 30 points on preoperative mini-mental test) or if there is a drop of more than 3 points compared to the value obtained preoperatively (in patients with a mini-mental preoperative test value less than 30 points).The incidence of postoperative surgical complications, which is defined as the presence of any of the complications during the first 30 days postoperatively, as follows:

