### Data collection and management

A data collection notebook (CRD) will be compiled with all the variables described. Patients will arrive at the operating room with the first sheet completed (including demographic, analytical, respiratory function, and preoperative morbidity information). During surgery, intraoperative information will be collected on the subsequent pages. Before registration, the CRD pages corresponding to the patient’s stay in the PCU will be filled out. The CRD information will be completed before discharge. The CRD will include the patient’s in-hospital medical history and information that is not computerized. At the time of discharge, it will be kept in a locked cabinet in the anesthesiology department and will be completed with the data obtained during the day-30 visit. Data from the CRDs will be entered into the computer program SPSS, where they will be reviewed and accepted by an external clinical research organization (CRO). This CRO will ensure compliance with the study procedure and will control the possible errors that may occur.

The criteria for withdrawal from the study are as follows:
The protocol procedures cannot be followed for medical reasonsTransfusion of intraoperative blood productsDuration of OLV less than 60 minAdverse events related to any medication that is used during the study that prevents the continuation of the protocolThe patient voluntarily decides to leave the study or withdraws informed consentAny adverse clinical event that requires withdrawal from the study in the opinion of the researcherCompletion of the study

Patients who have to withdraw from the study because of these criteria will not be replaced by other patients. From the moment at which the withdrawal from the trial is decided, study samples of inflammatory markers will no longer be obtained. These patients will be followed by the members of the research team in the same way as patients who complete the study until hospital discharge, guaranteeing them the same healthcare. In these cases, only safety data (serious adverse events) will be collected for the study. For patients who withdraw their consent, no further patient data will be collected in association with the trial from the moment they inform the research team.

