## Trial status

After we obtained the approval of the local ethics committee we included the first patient in the study on January 29, 2019. We plan to spend 30 months to include 153 patients and complete the trial in June 2021. Protocol number IGGFGG-2016 version 4.0 27th April 2017.

## Appendix 1

**Table 1 Tab1:** Clavien-Dindo classification

	Grade	Definition
Minor complications	I	Any complication without need for pharmacologic treatment or other intervention
	II	Any complication that requires pharmacologic treatment or minor intervention only
Major complications	III	Any complication that requires surgical, radiologic, endoscopic intervention, or multitherapy
	IIIa	Intervention does not require general anesthesia
	IIIb	Intervention requires general anesthesia
	IV	Any complication requiring intensive care unit management and life support
	IVa	Single organ dysfunction
	IVb	Multiorgan dysfunction
	V	Any complication leading to the death of the patient

## Appendix 2

**Table 2 Tab2:** Definition of postoperative pulmonary complications

Complication	Definition
Respiratory infection	When a patient received antibiotics for a suspected respiratory infection and met at least one of the following criteria: new or changed sputum, new or changed lung opacity, fever, leukocyte count > 12,000/μ
Respiratory failure	When postoperative PaO_2_ < 60 mmHg on room air, ratio of PaO_2_ to inspired oxygen fraction < 300 or arterial oxyhemoglobin saturation measured with pulse oximetry < 90% and requiring oxygen therapy
Pleural effusion	Chest X-ray demonstrating blunting of the costophrenic angle, loss of the sharp silhouette of the ipsilateral hemidiaphragm in upright position, evidence of displacement of adjacent anatomical structures, or (in supine position) a hazy opacity on one hemithorax with preserved vascular shadows
Atelectasis	Lung opacification with a shift of the mediastinum, hilum, or hemidiaphragm toward the affected area, and compensatory overinflation in the adjacent nonatelectatic lung
Pneumothorax	Air in the pleural space with no vascular bed surrounding the visceral pleura
Bronchospasm	Newly detected expiratory wheezing treated with bronchodilators
Aspiration pneumonitis	Acute lung injury after the inhalation of regurgitated gastric contents

## Appendix 3

**Table 3 Tab3:** Spirit figure

Visit	Visit 1 (day − 1)	Visit 2 (day 0)	Visit 3 (day 0)	Visit 4 (day 1)	Visit 5 (day 3)	Visit 6 (discharge)	Visit 7 (30 day)

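### The primary Clavien–Dindo grade has no stated time window and is adjudicated only at hospital discharge, which is not reconciled with the 30-day collection of complications, readmissions and deaths

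*Protocol article*

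**What the plan says.** **Primary outcome.** The Primary outcome section states: "The primary outcome is the proportion of patients included in the different scales of the Clavien–Dindo (C–D) classification". On what counts, it says: "Any deviation from a normal postoperative course will be classified into grade I, II (minor complications), IIIa, IIIb, IVa, IVb, and V (major complications"). It gives no end date, and neither does the Power calculation section, which returns to the same outcome.

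**Adjudication.** The section Adjudicating outcome variables says that "the C–D classification will be assessed separately by two teams of investigators (thoracic surgeons and anesthesiologists) at hospital discharge". The same sentence places the assessment of whether complications occurred at that time too. Disagreements go to a consensus meeting of the two teams. No other time for the grade appears in the article.

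**Thirty-day items.** For pulmonary complications, Secondary outcomes says: "The time frame is up to 30 days after intervention". Surgical, cardiac and renal complications and unplanned readmissions also run to 30 days. Adjudicating outcome variables adds: "Length of stay in the hospital and PACU, readmission, and mortality at 30 days will also be recorded", from the hospital's electronic register. Under Data collection and management, the data notebook is stored at discharge and "will be completed with the data obtained during the day-30 visit". The schedule in Appendix 3 marks both mortality and postoperative complications at Visit 7 (day 30).

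**Grade V.** Appendix 1, Table 1 defines it as: "Any complication leading to the death of the patient". No time limit is attached.

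**The concern.** A primary outcome should be observed over the same period in every patient, or the period should at least not depend on anything that happens after randomisation. A window that closes at discharge fails on both counts. Length of stay differs between patients, follows randomisation, and is compared between the arms as a secondary outcome. If stay differed by arm, patients in one arm would have fewer days in which a complication could count, whatever the treatment does to complications.

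Internal consistency is also at stake. Take a patient sent home at grade I who dies of a complication before day 30. That patient is a death in the 30-day mortality data, and a complication of that kind is grade V in Table 1. Yet a grade fixed at discharge stays at I. A readmission for empyema raises the same conflict with the surgical complication outcome.

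Finally, the same records allow two primary analyses, one on the discharge grade and one on a grade updated to day 30. The article does not say which is meant, so the choice could be made after results are known.

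**Working it through.** **1. The sections side by side**

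| Item | Time stated | Where in the protocol article |
|---|---|---|
| Primary C–D grade, definition | none | Primary outcome; Power calculation |
| Primary C–D grade, adjudication | hospital discharge | Adjudicating outcome variables |
| Pulmonary, surgical, cardiac, renal complications | 30 days | Secondary outcomes |
| Unplanned readmission | 30 days | Secondary outcomes |
| Mortality | 30 days | Adjudicating outcome variables |
| Blinded follow-up | one month | Randomization |
| Complications and mortality, last visit | Visit 7, day 30 | Appendix 3 |

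Every complication item has a 30-day horizon except the grade that summarises them. No section says that day-30 data update the grade, and none says that they do not.

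**2. The plan's own sample size**

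Inputs from Power calculation: difference 1 unit, SD 1.5, two-sided alpha 0.05, power 0.90, losses 5%.

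- n per group = 2 × (1.960 + 1.282)² × 1.5² / 1² = 47.3, rounded up to 48.
- 48 / 0.95 = 50.5, rounded up to 51; 3 × 51 = 153.
- Power at 48 per group is 0.904.

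Both stated figures reproduce. None of these inputs refers to a window, so fixing the window at 30 days leaves 48 and 153 as they are.

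**3. What could be lost: illustrations on assumptions that are not in the documents**

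*Dilution of a real effect.* Assume that the SD stays at 1.5 and that a discharge-only grade captures a fraction f of a true 1-unit difference at day 30. Power at 48 per group is then:

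| f | 1.0 | 0.95 | 0.9 | 0.8 | 0.7 |
|---|---|---|---|---|---|
| Power | 0.904 | 0.873 | 0.836 | 0.743 | 0.628 |

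*Unequal windows with no true effect.* Assume stays of 4 and 6 days in two arms and a constant daily hazard h, so that the share with a complication counted is 1 − exp(−h × days).

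- h = 0.01: 3.9% against 5.8%, a gap of 1.9 percentage points.
- h = 0.02: 7.7% against 11.3%, a gap of 3.6 points.

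If each such event scored 2 units (grade II, also assumed), the mean grade would shift by 2 × 0.019 = 0.04 to 2 × 0.036 = 0.07 units. The standard error of a two-arm difference is 1.5 × √(2/48) = 0.31. On these assumptions the shift is small. The model also treats stay as unaffected by complications, although complications prolong stay.

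**The case against.** The strongest reply is that the article does not exclude post-discharge events. The notebook is completed with day-30 data, the schedule records complications and deaths at Visit 7, blinded follow-up runs to one month, and neither the primary outcome definition nor grade V carries a cut-off at discharge. The adjudication sentence also puts the assessment of complications at discharge, although those outcomes are defined to 30 days, so it may not describe the whole process. This stands. A reader might infer that a patient readmitted, or dying after discharge, definitely keeps the discharge grade. The documents do not settle that. A death in hospital counts on any reading.

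A reader might also infer that the protocol expects lidocaine to shorten stay and that the outcome is therefore tilted towards lidocaine. The Background does mention "a shorter duration of postoperative paralytic ileus, and earlier hospital discharge", but as a finding of earlier work on intravenous lidocaine. The trial's own hypothesis is an attenuated inflammatory response and a better postoperative course. Length of stay is a secondary outcome with no predicted direction, and all arms share one postoperative protocol. A bias favouring lidocaine is thus not supported.

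These replies do not supply a window for the primary grade. If the grade is updated after discharge, the article describes no two-team assessment or consensus step for the later events.

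**Conclusion.** The point holds as an inconsistency in the definition of the primary outcome. The grade has no stated window, discharge is its only stated adjudication time, and this is not reconciled with 30-day collection of the events that it should summarise. Followed as written, the window depends on length of stay, and post-discharge complications or deaths are lost from the primary comparison unless the grade is adjudicated again.

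This is more than detail left out by a condensed article, because the article does state a time and that time conflicts with its other sections. The effect on the result cannot be sized or given a direction: no length of stay, post-discharge event rate or day-30 SD is stated. The figures above show what particular assumptions would imply and are not estimates for this trial. No stated sample-size figure is in dispute.

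**What to change.** Define the primary outcome as the highest Clavien–Dindo grade reached from surgery to day 30. Have both blinded teams assign it after Visit 7, with the existing consensus step, counting complications and readmissions after discharge. A complication that leads to death by day 30 is grade V. Keep the causal link to a complication, since Table 1 does not make every death grade V. A discharge grade may be kept as an interim record.

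One further rule must be aligned. Under Data collection and management, withdrawn patients are followed to discharge and only serious adverse events are collected, while Statistical analysis promises intention to treat. Withdrawn patients who have not withdrawn consent should also contribute a day-30 grade.

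Cost: the visit, data capture and assessors already exist. Adjudication is completed about a month after surgery instead of at discharge, and patients withdrawn from treatment need outcome data to day 30. The stated sample-size inputs are unchanged. The change should be documented before unblinding.

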Surgeons and anesthesiologists have used many classifications to perform clinical studies comparing the impact of measurements used in the pre-, intra-, or postoperative period. However, the overall impact on the postoperative course has not been taken into account. Most of the studies that analyze PPCs make a composite variable that comprises all the complications that affect the respiratory tract but have very different severity and impact on the postoperative course. For example, the presence of cough, suspicion of infection, pulmonary edema, and subsegmental atelectasis are usually included as PPCs. However, the clinical relevance of these complications is much lower than that of other PPCs, such as pneumonia, lobar atelectasis, or adult respiratory acute syndrome (ARDS). Thus, it is not surprising that there are studies that describe a similar hospital stay between groups despite observing a different incidence of PPCs related to an intervention because certain complications have little effect on the postoperative treatment provided to the patients. This occurs in studies in which all postoperative complications are presented as a single composite variable without taking into account the severity of each of complication. In our research, we want to determine the real impact on the postoperative course of using IV or PV lidocaine. Thus, we will use the C–D classification to rate the postoperative complications and evaluate the intensity of therapeutic measures that are not routinely included within the normal postoperative course.

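### The consensus meeting applies a diagnostic filter that the Clavien-Dindo primary outcome does not have, so a treated event can be dropped where the two teams disagree and kept where they agree

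*Protocol article*

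**What the plan says.** The Primary outcome section ties the grade to treatment: "The greater the intensity of the treatment that is necessary to correct any postoperative complication, the higher the C–D classification will be considered". Its scope is broad: "Any deviation from a normal postoperative course will be classified into grade I, II (minor complications", and so on up to grade V. Appendix 1 (Table 1) follows the same logic; grade II, for example, is "Any complication that requires pharmacologic treatment or minor intervention only". Neither place asks that the event satisfy a diagnostic definition.

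The section Adjudicating outcome variables sets out how outcomes are judged: "The presence of postoperative complications and the C–D classification will be assessed separately by two teams of investigators", at hospital discharge. Then: "In cases of discrepancy, there will be a meeting between both teams to discuss the results and reach an agreement". At that meeting each collected complication is checked against the criteria for its diagnosis. Those that satisfy the criteria are recorded, and "those that do not meet the definition criteria will not be evaluated".

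The diagnostic definitions that the article gives are in Secondary outcomes (surgical, cardiac, renal and cognitive events) and in Appendix 2 (pulmonary events). The Discussion explains that the scale was chosen to "evaluate the intensity of therapeutic measures that are not routinely included within the normal postoperative course", in preference to composites of diagnoses.

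**The concern.** Two rules bear on the same endpoint. One grades by treatment and needs no diagnosis. The other removes events that miss a diagnosis, and it sits in a paragraph that expressly covers the Clavien-Dindo grade. No sentence exempts the grade from the filter.

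The filter is also attached to the meeting, and the meeting takes place only after a discrepancy. Whether a given treated event counts could therefore depend on whether two teams happened to differ, rather than on what happened to the patient. The wording also leaves open what follows removal: the patient might be scored as having no complication, or keep a lower grade from another event. At stake are the consistency of the primary endpoint and the stated reason for using this scale.

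**Working it through.** The point concerns an outcome rule, so the main check sets the texts side by side.

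**Planned sample size.** This reproduces and is not in dispute. From Power calculation: SD 1.5, difference 1 unit, two-sided alpha 5%, beta 10%.

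- n per group = 2 × (1.960 + 1.282)² × 1.5² / 1² ≈ 2 × 10.51 × 2.25 ≈ 47.3, rounded up to 48.
- Allowing for 5% losses: 48 / 0.95 = 50.5, rounded up to 51; 3 × 51 = 153.

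**What decides whether an event counts**

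| Place | Test applied | When |
|---|---|---|
| Primary outcome; Appendix 1 | Departure from a normal course, graded by treatment needed | All patients |
| Adjudicating outcome variables | Meets the criteria for its diagnosis; otherwise not evaluated | Meeting after a discrepancy |

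**A case worked through.** Appendix 2 counts a respiratory infection only if antibiotics were given for a suspected infection and at least one further criterion was present: a sputum change, a lung opacity change, fever or a raised leukocyte count. Take a patient who received the antibiotics and had none of these.

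1. Under the Primary outcome section and Appendix 1, drug treatment was required, so the event is grade II.
2. If both teams record it and agree, no meeting is called, the filter is never reached and grade II stands.
3. If one team records it and the other does not, the meeting is held. The event fails its Appendix 2 definition and is not evaluated.

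The same event under the same treatment gives two results.

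**Could the definition criteria be those of the Clavien-Dindo scale itself?** This is not the natural reading. The sentence speaks of criteria for diagnosis, and the scale grades treatment. The diagnostic criteria in the article are those in Secondary outcomes and Appendix 2.

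**Can the loss be sized?** The share of events removed from the primary outcome would be

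share removed = (share of events reaching the meeting) × (share of those that fail their definition).

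The document gives neither factor, nor the expected distribution of grades by group. No numerical effect on the difference, or on power, follows from it.

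**The case against.** The strongest reply is that the adjudication paragraph covers two tasks, diagnosing complications and grading them, and that the filter belongs only to the first. On that reading the definitions govern the secondary endpoints, the Primary outcome section governs the grade, and nothing is deleted. The full protocol, which is not shown, may say so. This reading is possible, and it may be what the investigators intend, but the article does not state it. Both tasks are named as one process and the exclusion is worded without limit. A team following the text could drop the event.

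Other parts of the reply stand and limit the point:

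- **The example is narrow.** Any one of four further criteria rescues the event.
- **Severe events are largely protected.** Re-operation for any reason is a listed complication, and 30-day mortality is taken separately from the hospital register.
- **Unlisted events.** A reader might infer that every treated event outside the article's lists is lost. The text refers to criteria for diagnosis and does not confine these to the printed lists, so a closed list is an inference.
- **Operated-side pneumothorax or effusion.** A reader might also infer that these are struck from the primary outcome, because "we will consider them to be complications only if they occur in the dependent lung". That restriction is stated for the secondary pulmonary endpoint and concerns findings described as usual after this surgery, which arguably are not departures from a normal course. The Appendix 2 definitions carry no side restriction. The document does not support using these events as an example of deletion.

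**Conclusion.** The point holds as an inconsistency in the rule for the primary endpoint. Following the text, a treated deviation that misses its diagnostic definition can be removed in patients on whom the teams disagree and kept where they agree. This runs against the rationale in the Discussion. The conclusion assumes that the filter applies to the grade as well as to the diagnosis, which the shared paragraph permits and nothing excludes.

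Two stronger conclusions are not supported:

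- **Bias towards one group.** All outcome assessors are stated to be blinded to allocation, so no direction is shown. Dilution of a true difference is possible, but only so far as the removed events are ones the treatment would have prevented.
- **A stated loss of power.** Any figure would need an invented deletion rate, and one applied to all events would ignore that only discordant cases reach the meeting.

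The extent is unknown and may be small. The point merits correction because it touches the primary outcome and costs almost nothing to settle, not because the trial's conclusions are shown to be at risk.

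**What to change.** Before unblinding, reconcile the adjudication paragraph with the Primary outcome section by stating that:

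1. the diagnostic definitions decide only which secondary complication endpoint an event counts towards;
2. the primary Clavien-Dindo grade is given to every departure from the normal course according to the treatment received, whether or not a diagnostic definition is met;
3. the consensus meeting settles the grade and does not delete a treated deviation for failing a definition;
4. the same rule applies whether or not the two teams first agreed.

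The investigators should also say whether the dependent-lung restriction in Secondary outcomes applies to Clavien-Dindo grading. That is for them to decide.

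The cost is a few sentences and slightly more events to grade. No new data, visits or assessors are needed, since the meeting already reviews the collected complications and the schedule in Appendix 3 records them to day 30. The sample size is unchanged.
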